### 2.5. Procedure

#### 2.5.1. MBSR-P and Implementation

For this research, the MBSR program created by Jon-Kabat Zinn et al. in 1979 at the University of Massachusetts will be applied, with some adaptations. The MBSR is a psychoeducational intervention program that has mindfulness as its backbone, and whose objective is to provide strategies for the management and awareness of stress itself. It is an instructive and multimodal intervention that is carried out in a systematic and structured manner [59].

The original MBSR program lasts 8 weeks, with weekly sessions of 2.50 h, along with an intensive day of 6 h and daily homework of 45 min, with the aim of integrating the practices and generalizing them to daily life. Intervention groups typically range from 10 to 40 participants [13,19].

As mentioned above, taking into account the implementation context, the target population, and their circumstances, a series of adaptations will be made to the original MBSR program, as indicated [64]. The adaptations will be aimed at the timing of the intervention, the informal practices, and the contents. Regarding the timing of both the formal sessions and the recommended informal practices, the required duration will be reduced. The formal MBSR-P sessions will last 1.50 h (except for the informative session, which will last 2 h, and the intensive session, which will last 3 h), and the home practices will last 30 min. Concerning the contents’ adaptation, two specific sessions dedicated to promoting positive parenting will be incorporated. Therefore, the complete program will consist of 11 sessions: a first informative session, 8 weekly sessions based on MBSR, and 2 positive parenting sessions aimed at promoting parenting adapted to the children’s needs as well as awareness of their own parenting practices. The program includes home practices each week. The home practices will be introduced in the last part of each session, and the necessary materials to be able to carry them out will be sent via email. The program is expected to have a total duration of 3 months.

Thus, the rationale behind how the program is organized is that throughout the eight MBSR-based sessions parents will work on activating their internal resources which, in turn, will help them to cope with the challenges they face in their daily lives in their parenting roles. In addition, the home practices and the group dynamics will allow parents to implement what they have learned in the different sessions in their family lives and, particularly, in their parental roles. The last two specific positive parenting sessions will have a complementary role in terms of reinforcing the application of the strategies and resources learned in the previous sessions in their parenting roles, and will provide the parents with additional strategies to cope with their situations and attend to specific needs, such as communication difficulties.

In all sessions, a specific structure will be followed: the session will begin with a group meditation; later, time will be dedicated to sharing the home practices from the previous week, and individual experiences will be presented in the large group; then, the contents planned for the session will be introduced, and will be practiced through meditations and other exercises, which will also be done in small groups; finally, in the last part of the session, the home practices planned for that week will be presented. The sessions will finish with a group meditation. Table 1 presents the detailed contents of each session.

Regarding the materials required to carry out the practices in the formal sessions, it will be necessary to have a large space equipped with mats and chairs for each participant, so that they can perform every type of meditation comfortably. The necessary materials to carry out the home practices (audios, videos, readings, schemes) will be provided by the professional responsible for the group.

#### 2.5.2. Process Evaluation

In the first meeting, the participants will be informed about how the program will be carried out, the general objectives of the program, their participation in it, the content of the sessions, the importance of their engagement with all of the sessions, the materials that will be needed, and the guidelines to follow throughout the process, such as carrying out activities at home. Once the information has been received and any doubts clarified, if they agree with all of the points, the participants will sign an informed consent form in accordance with the Declaration of Helsinki [65], in which they will be informed that the discussion group will be audio recorded, and that confidentiality will be ensured for all participants. The informed consent will also notify the participants that they can leave the intervention at any time without this decision having any consequences. There will be no financial or other incentives for participation.

In this first session, the pre-test data from the battery of self-administered questionnaires will be collected (including both the sociodemographic profiles and the effectiveness measures) from the intervention group. In the intermediate phase of the intervention (sixth session), the participants will fill out the questionnaire to evaluate the feedback of the intervention process up until that moment. At the end of the intervention, the post-test data from the battery of effectiveness and satisfaction self-administered questionnaires will be collected, and the discussion group will be held. Furthermore, during the intervention process, after each session, the professional in charge of the implementation will fill out the field diary corresponding to each session once the session is over. Over a period of 6 months after the end of the intervention, the follow-up will be carried out, in which the battery of instruments referring to the effectiveness of the intervention will be administered to the participants, in addition to the follow-up questionnaire aimed at evaluating the application to daily life of the learning achieved through participation in the intervention.

The control group will fill out the pre- and post-test batteries of questionnaires (sociodemographic profiles and effectiveness measures) in a comparable time frame to the intervention group. This data collection will be carried out under the same terms, conditions, and time periods as in the intervention group. Two people will be involved in the data collection, both with prior training in the collection and analysis of both quantitative and qualitative data. During the completion of the questionnaires, any doubts that may arise will be clarified individually to eliminate bias.

In relation to the confidentiality of the data, each person will be assigned identifiers to archive them, and secure cloud content management software will be used to save the data.

Figure 1 shows the evaluation process that will be carried out—specifically, what information will be collected at each moment.

#### 2.5.3. Sample Size

To calculate the sample size necessary to achieve adequate statistical power in the evaluation of the program, the G*Power 3.1 program was used [66]. Two calculations were made for the sample size. The first calculation that was carried out for the pre-test and post-test analyses was made a priori for ANOVA analysis of repeated measures within–between interaction, with a mean Cohen effect size *f* = 0.25 [67] and α = 0.05, two groups with two temporal measures, correlation between the measures of 0.50, and sphericity of 1. With these assumptions, to achieve the acceptable minimum Cohen effect size of 0.80 [68] and obtain a statistical power of 0.80, the sample should consist of at least 34 participants. Although regarding the size of the control group, following a common knowledge rule in program evaluation, the control group should be composed of a minimum of (*n*/2) + 1—where *n* is the sample size of the group of participants—in this study, a minimum of 20 participants is established for the control group, with the objective of reaching the recommended size for the parametric tests [69].

The second sample calculation that was carried out for the follow-up analysis of the intervention group was performed a priori for the ANOVA analysis of repeated measures within factors, with a mean Cohen effect size *f* = 0.25 [67] and α = 0.05, a group with three temporal measures, correlation between the measures of 0.50, and sphericity of 1. With these assumptions, to achieve the acceptable minimum Cohen effect size of 0.80 [68] and obtain a statistical power of 0.80, the sample should be made up of at least 28 participants.

Among the analyses that were conducted, the most restrictive was the first calculation referring to pre-test and post-test measures of the intervention group and the control group; thus, we assume that the study sample must consist of at least 34 participants for the intervention group and 20 participants for the control group.

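### The sample-size section gives the two-group total of 34 to the intervention arm alone, names the wrong calculation as binding for that arm, and states an effect size of 0.80 that contradicts f = 0.25; the error is conservative

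*Protocol article*

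**What the plan says.** All of this is in the protocol article, section 2.5.3 (Sample Size), which reports that "the G*Power 3.1 program was used" for two calculations.

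- **Calculation 1** (pre-test and post-test, both groups) was "made a priori for ANOVA analysis of repeated measures within–between interaction", "with a mean Cohen effect size *f* = 0.25 [67] and α = 0.05", and "two groups with two temporal measures, correlation between the measures of 0.50, and sphericity of 1". With a power of 0.80 it gives a sample of at least 34.
- **Calculation 2** (follow-up, intervention group only) uses the same f, alpha, correlation and sphericity with one group and three measures. It concludes that "the sample should be made up of at least 28 participants".
- Each calculation also carries the phrase "to achieve the acceptable minimum Cohen effect size of 0.80", directly beside the power of 0.80.
- The control group is set at a minimum of 20. The section mentions an (n/2) + 1 rule of thumb, but the reason it gives for 20 is a recommended size for parametric tests.
- The section closes: "Among the analyses that were conducted, the most restrictive was the first calculation", and it therefore assumes that "the study sample must consist of at least 34 participants for the intervention group and 20 participants for the control group".

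**The concern.** For a within–between interaction with two groups, the sample size that reproduces from these inputs counts all participants in both groups. The closing sentence treats it as the size of one arm and adds controls fixed on other grounds. The ranking of the two calculations then compares a two-group total (34) with a one-group size (28), which are not the same quantity. The stated effect of 0.80 makes it unclear what the study is sized to detect.

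Three things are at stake:

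- The section never reports the power of the allocation it adopts, 34 + 20.
- A reader who follows the closing sentence would take the pre–post comparison as the tight constraint on the intervention arm. The tight one is the 6-month analysis, and section 2.6.1 discards cases with missing data at the questionnaire level.
- Two incompatible effect sizes are given for the same calculation.

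**Working it through.** **Inputs (section 2.5.3).** f = 0.25; alpha = 0.05; correlation rho = 0.50; sphericity epsilon = 1; target power 0.80. Calculation 1: k = 2 groups, m = 2 measures. Calculation 2: k = 1, m = 3.

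**Formula.** Noncentral F for repeated measures, with N the total over all groups:

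lambda = f² × N × m × epsilon / (1 − rho)

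- Interaction: df1 = (k − 1)(m − 1), df2 = (N − k)(m − 1).
- Within factor: df1 = m − 1, df2 = (N − k)(m − 1).

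**Step 1: reproduce 34.** At N = 34, lambda = 0.0625 × 34 × 2 / 0.5 = 8.5, with df 1 and 32.

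| Total N | Power |
|---|---|
| 32 | 0.781 |
| 33 | 0.795 |
| 34 (17 + 17) | 0.807 |
| 68 (34 + 34) | 0.982 |

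So 34 is the smallest total that reaches 0.80. The alternative effect-size convention (the SPSS-type option) gives power of only 0.28 at N = 34, so it does not explain the figure.

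**Step 2: reproduce 28.** At N = 28, lambda = 0.0625 × 28 × 3 / 0.5 = 10.5, with df 2 and 54.

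| Intervention n | Power |
|---|---|
| 24 | 0.741 |
| 27 | 0.796 |
| 28 | 0.812 |
| 34 | 0.888 |

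So 28 is right for one group.

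**Step 3: power of the adopted allocation.** With f = 0.25 the between-group difference in change is 4 × f × sigma = 1.0 sigma. The variance of a change score is 2(1 − rho) sigma² = 1.0 sigma². For unequal groups:

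lambda = 16 f² / [2(1 − rho)(1/n1 + 1/n2)], with df 1 and n1 + n2 − 2.

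As a check, 17 + 17 gives lambda = 1 / (2/17) = 8.5, as in Step 1. For 34 + 20, lambda = 1 / (1/34 + 1/20) = 12.59.

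| Intervention + control | Interaction power |
|---|---|
| 14 + 20 | 0.795 |
| 15 + 20 | 0.811 |
| 24 + 20 | 0.897 |
| 28 + 20 | 0.917 |
| 34 + 20 | 0.936 |

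With 20 controls, calculation 1 needs 15 intervention parents. Calculation 2 needs 28, so it sets the minimum for that arm.

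**Step 4: margin for loss.** 34 − 28 = 6, and 6/34 = 17.6%. A seventh loss leaves 27 and power 0.796. As an illustration only, since the article gives no dropout figure: with 24 of 34 remaining, the interaction keeps power 0.897 while the follow-up test falls to 0.741.

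**Step 5: the 0.80 effect size.** If f were 0.80, calculation 1 would need 6 participants in total (power 0.83). Read instead as a standardised difference of 0.8 between two independent means, it would need about 25 per group (normal approximation). Neither gives 34.

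**Step 6: sensitivity.** Varying rho (assumed range) at 34 + 20 with f = 0.25, interaction power is about 0.84 at rho = 0.3 and 0.99 at rho = 0.7. If the true difference in change were 0.5 sigma at rho = 0.50 (assumed; f = 0.125), lambda is 12.59 / 4 = 3.15 and power about 0.41.

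**The case against.** The strongest reply is that no harm follows. The section sets minimums to reach 0.80, and 34 + 20 meets both targets with room to spare. The misassignment also raises the intervention arm above 28 and so creates the margin of six. This stands, and it limits the point to a correction of the text.

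A second reply is that 34 is larger than 28 when both are read as bare software outputs, so the ranking is true in that sense and its error only follows from the misassignment. That is fair as to origin. But the section uses the ranking to fix the size of one arm, and for that arm it is wrong.

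A reader might infer more than the text supports:

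- **That the study is underpowered.** It is not, under the stated inputs.
- **That 20 controls conflict with the (n/2) + 1 rule.** With n = 34 the rule gives 18 as a minimum, which 20 satisfies, and the section gives a different reason for 20.
- **That the requirement of 28 is concealed, or that the first calculation is said to cover everything.** Calculation 2 is printed with its inputs and result, and no such claim is made.

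A last caution also stands: quoting power of 0.94 without the effect behind it would reassure too much, because f = 0.25 here means a full standard deviation of difference in change.

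**Conclusion.** The point holds as a correction to section 2.5.3. The stated 34 is a two-group total given to one arm. Calculation 2, not calculation 1, sets the intervention arm's minimum (28 against about 17, or 15 with 20 controls). The minimum effect size of 0.80 contradicts f = 0.25 and looks like the power target repeated.

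The direction is conservative: full enrolment gives about 0.94 for the interaction and 0.89 for the follow-up test, against a target of 0.80. These figures rest on f = 0.25, rho = 0.50, sphericity and complete data. No analysis or enrolment target needs to change, but the size, effect and power as printed do not describe one design.

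**What to change.** Reword section 2.5.3 as follows:

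- State that calculation 1 requires 34 participants in total, 17 per group.
- State that calculation 2 requires 28 intervention parents with complete 6-month data and sets the minimum for that arm. Enrolling 34 then allows at most 6 losses (17.6%) before follow-up power drops below 0.80.
- Report the power of the adopted 34 + 20 (about 0.94 for the interaction) together with its assumption: f = 0.25 with rho = 0.50, equivalent to a 1.0 SD between-group difference in change.
- Delete the minimum effect size of 0.80 in both calculations, leaving f = 0.25 as the effect and 0.80 as the power.
- Say that the 20 controls do not come from the power calculation. The (n/2) + 1 rule may stay.

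The cost is a few sentences; enrolment is unchanged.

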### 2.6. Data Analysis

#### 2.6.1. Quantitative Data

The analysis of the quantitative data will be carried out using the statistical program SPSS v-21 (IBM Corp., Armonk, NY, USA) [70]. Firstly, missing data at the level of the Likert scale questionnaires will be studied. Little’s MCAR test will be used to verify whether missing data per questionnaire are below 10%, which will mean that they are randomly distributed. If this assumption is met, it will also be verified whether missing data per item have a percentage below 5% and, if so, the data will be imputed through the SEM procedure using the expectation maximization (EM) algorithm from SPSS. For those cases with missing data at the questionnaire level, the cases will be discarded [71].

The distribution of the values will also be evaluated through asymmetry and kurtosis, and the presence of extreme cases in the variables studied will be examined by analyzing the interquartile ranges through stem and leaf graphs [72].

Moreover, other statistical assumptions for the parametric tests will be checked and reported (i.e., sphericity, normality, linearity, homogeneity, and absence of multicollinearity and singularity) [73]. If the sphericity assumption is not fulfilled, the *F*-test will be adjusted as an alternative for analysis with the Greenhouse–Geisser index, reducing the degrees of freedom associated with the *F* statistic of the ANOVA as a function of the corrective factor ε [74]. If normality violation occurs, parsimony transformations will be applied to correct the non-normal distributions [75]. If multicollinearity applies, composited factors will be computed for those involved variables.

The sociodemographic variables will be used to describe the samples, to control for them in the main analyses, and to achieve equivalence between the characteristics of the control group and those of the intervention group. Both descriptive and correlational analyses will be performed as preliminary analyses.

The effectiveness of the MBSR-P intervention will be examined by performing two-way repeated measures ANOVA for each effectiveness dimension studied, with the group (0 = *control*, 1 = *intervention*) as the factor. Interaction effects will be examined. *R*^2^ will be computed as the effect size index, and will be evaluated according to the conventional levels of 0.01, 0.06, and 0.14 for the small, medium, and large effect size levels, respectively [67]. The corrected *R*^2^ will be calculated taking into account the within- and between-subjects errors [75]. In the event that the assumptions for these analyses are not fulfilled (e.g., if normality is violated and not able to be fixed by variable transformations), Wilcoxon’s non-parametric tests will be used as an alternative [74]. Mean and standard deviation will be provided for participants’ satisfaction, and for the implementation of information registered in the field diaries.

Figure 2 shows the steps that will be followed for quantitative data analysis.

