11	Specific positive parenting session: Parenting practices related to establishing limits without being authoritarian, adapting those practices to the developmental period of their children and the importance of negotiation, particularly during adolescence. Focus on self-regulation and expectations as key elements to avoid the escalation of possible conflictive situations. Role-playing of emerging situations related to their parenting roles. For example, a common emergent situation would be a child arriving home after curfew. Parents represent those situations and work on how to avoid reacting rather than responding, how to handle their emotions, and how to be aware of their own and their child’s responses. Post-test effectiveness and satisfaction instruments battery and discussion group.

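### A missingness rate below 10% is wrongly read as random loss, and discarding parents with a missing questionnaire makes every effectiveness result completers-only

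*Protocol article*

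**What the plan says.** All of the missing-data text is in section 2.6.1 of the protocol article.

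- **Randomness check:** "Little’s MCAR test will be used to verify whether missing data per questionnaire are below 10%, which will mean that they are randomly distributed".
- **Item-level gaps:** when that condition holds and fewer than 5% of values are missing per item, "if so, the data will be imputed through the SEM procedure using the expectation maximization (EM) algorithm from SPSS".
- **Whole questionnaires:** "For those cases with missing data at the questionnaire level, the cases will be discarded".
- **Main analysis:** effectiveness is examined by "performing two-way repeated measures ANOVA for each effectiveness dimension studied", with group as the factor and attention to the interaction.

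Three other places bear on who will be missing.

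- Table 1 puts the intervention group's post-test inside session 11, the last one: "Post-test effectiveness and satisfaction instruments battery and discussion group".
- Section 2.5.2 tells parents that "they can leave the intervention at any time without this decision having any consequences".
- Section 2.5.2 also gives controls a pre-test and a post-test battery on comparable timing. It describes no 6-month battery for them.

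The sample size in section 2.5.3 (34 intervention, 20 control) has no stated allowance for loss.

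**The concern.** There are two distinct problems, and they should be kept apart.

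**The inference.** Little's test returns a p-value against the hypothesis that data are missing completely at random. It does not test whether a percentage is under a threshold. Nor does a small percentage say why values are missing: a few gaps can be entirely systematic. The consequence is limited, because the sentence controls only whether isolated items are imputed by EM.

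**The discard.** A repeated measures ANOVA needs every occasion, and the plan removes cases that lack a questionnaire. The text leaves open whether the parent leaves the whole study or only the affected outcome. Either way, the group-by-time effect for that outcome is estimated from parents who supplied both scores. That estimate is unbiased only if loss is unrelated to baseline and to change. The post-test sits in the final session of an 11-session programme that parents may leave, so those who stop attending are the likeliest to be absent. Waiting-list controls have no sessions to stop attending, so loss is probably unequal between groups. What is at stake is the second objective: the effect of the programme in the parents enrolled, not only in those who stayed.

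**Working it through.** **1. Reproduce the plan's sample sizes.** Inputs from section 2.5.3: f = 0.25, α = 0.05, correlation ρ = 0.50, sphericity 1, power 0.80.

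- Pre/post interaction, 2 groups and m = 2 occasions: λ = f²·N·m/(1−ρ) = 0.0625 × 34 × 2 / 0.5 = 8.5, with 1 and 32 df. Power is 0.807, so N = 34 reproduces.
- One group, m = 3 occasions: λ = 0.0625 × 28 × 3 / 0.5 = 10.5, with 2 and 54 df. Power is 0.812, so N = 28 reproduces.

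**2. Power after discarding.** For unequal groups, λ = n₁n₂/(n₁+n₂). With equal groups this is N/4, the same as step 1 (34/4 = 8.5). The loss rates are assumptions; the protocol gives none.

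| Loss in both groups | n₁/n₂ | λ | Power |
|---|---|---|---|
| 0% | 34/20 | 680/54 = 12.59 | 0.94 |
| 10% | 31/18 | 558/49 = 11.39 | 0.91 |
| 20% | 27/16 | 432/43 = 10.05 | 0.87 |
| 30% | 24/14 | 336/38 = 8.84 | 0.83 |
| 40% | 20/12 | 240/32 = 7.50 | 0.76 |

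The three-occasion analysis of 34 intervention parents is tighter: 0.85, 0.80 and 0.74 at 10, 20 and 30% loss.

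**3. Does a rate below 10% show randomness?** Little's test was simulated on 200 datasets with n = 54 and 5 items, one item missing for 11 people. That is 11/270 = 4.1% of cells. The test rejected in 5% of datasets when the gaps were random and in 100% when they depended strongly on the other items. The rate was the same in both settings, so it cannot tell them apart.

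**4. Bias from discarding.** Assumptions: no true effect, scores with SD 1, ρ = 0.50 as in the plan, loss in the intervention group only, and odds of loss multiplied by 3 per SD of whatever drives it. A higher score is worse, as for stress. The figures are the mean change in the parents retained, when it should be zero.

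| Intervention loss | Random loss | Loss follows worsening | Loss follows high baseline |
|---|---|---|---|
| 10% | 0.00 | 0.10 towards benefit | 0.05 against benefit |
| 20% | 0.00 | 0.18 towards benefit | 0.09 against benefit |
| 30% | 0.00 | 0.27 towards benefit | 0.14 against benefit |

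The high-baseline case runs against benefit because the parents removed are those who would have regressed downwards.

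**5. What a likelihood-based model recovers at 30% loss.** With two occasions it removes the baseline-driven bias entirely. When loss follows worsening, about 0.21 of the 0.27 SD remains, because the model adjusts only for what baseline predicts. Obtaining the missing post-tests is therefore the remedy with most effect.

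**The case against.** Several replies are fair.

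- **One-sided loss and inflated benefit.** A reader might infer that only intervention parents are lost and that the result is pushed towards benefit. The documents support neither as fact. The discard rule applies to both groups, controls can also fail to return a battery, and nothing says an absent parent is refused the post-test. Section 2.4.2 gives priority to parents referred by professionals and seeks those with higher support needs. Loss of high-baseline parents is therefore plausible, and that bias runs the other way.
- **Power.** A reader might infer that discarding leaves the pre/post comparison underpowered. For a 0.8 SD difference in change, power does fall from 0.80 (34/20) to 0.70 (27/16). But the plan's f = 0.25 with ρ = 0.50 corresponds to 1.0 SD, for which the figures are 0.94 and 0.87.
- **The Little's test sentence.** It does not license the discard, and it could be carried out: both the rate and the p-value can be computed. Only the conclusion drawn is wrong.
- **Limits of the remedy.** A mixed model alone leaves most of the bias when loss follows unobserved worsening. This reply stands, and it sets the emphasis of the fix.

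None of this rescues the two rules. Both are stated in the text, so they are not details left to an analysis plan, and the article names no analysis that keeps parents with a missing questionnaire.

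**Conclusion.** The point holds in this form. The clause equating a rate below 10% with random distribution is wrong, though its reach is confined to item-level imputation. The discard rule makes each effectiveness result completers-only, under either reading of what a discarded case is. Selective loss is likely from where the post-test is placed, but its direction is unknown. At 30% intervention-only loss the bias is about 0.27 SD towards benefit or 0.14 SD against it, depending on what drives loss. Those sizes rest on assumed loss rates and selection strengths; under random loss the bias is nil. Pre/post power is not the main concern at the plan's own effect size. This should be fixed. It is a correctable weakness in a design whose non-randomised nature the authors already acknowledge.

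**What to change.** 1. Delete the clause that equates below 10% with random distribution. Report the missingness rate and the Little's test p-value separately, and do not treat a non-significant result as proof of randomness.
2. Offer the post-test battery to all consented parents in both groups, and the 6-month battery to all consented intervention parents, whatever their attendance. This matters most, because it recovers what no model can.
3. Replace discarding by a linear mixed model (available as MIXED in the SPSS software already named) with group, time and group × time, using every enrolled parent who has any score. State that it is valid if data are missing at random, and that it does not remove bias from loss that depends on unobserved change.
4. Keep the completers analysis as a sensitivity analysis, and add one that assigns no change to drop-outs. EM can remain for isolated missing items.

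The cost is some rewording, a few questionnaires collected outside the session, and slightly more analysis. No extra recruitment is needed for this point.
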